**Figure 1 F1:**
[figure not shown]
Flow diagram showing the process of the intervention.

Additionally, participants will be asked to avoid physical activity for at least 48 h prior to the study, to ensure baseline resting metabolic state.

#### Day 0: familiarization

2.5.1

During the week prior to DOMS induction and intervention, all participants will attend a familiarization session to become acquainted with the procedures, practice the exercises, undergo an initial graded exercise test to determine VO_2_max, and complete an initial hypoxia trial session. This trial allows the Mitovit device to assess each participant's physiological profile.

#### Day 1: DOMS induction

2.5.2

Before the DOMS induction, baseline measurements in normobaric conditions will be performed.

The exercise protocol to induce hamstring DOMS through eccentric contractions will include the following exercises: Nordic Hamstring Exercise (5 sets × 5 reps, rest = 90 s); Bilateral Leg Curl (5 sets × 8 reps, 80% 1RM, rest = 90 s); Romanian Deadlift (5 sets × 8 maximal reps, rest = 90 s), and Bilateral Leg Curl eccentric phase only (5 sets × 8 reps, 130% 1RM, rest = 90 s). This protocol was designed based on previous studies (21).

The selected protocol emphasizes high-volume and high-intensity eccentric contractions of the hamstring muscle group, which have consistently been shown to induce exercise-induced muscle damage and delayed onset muscle soreness in physically active individuals (21). Similar eccentric-based protocols have demonstrated reproducible increases in muscle soreness, reductions in strength, and alterations in functional performance within 24–72 h post-exercise (4, 21).

To confirm the success of DOMS induction, subjective measures of muscle soreness and objective neuromuscular performance will be assessed at baseline and daily throughout the intervention period (4). A clinically significant increase in perceived muscle soreness, along with concomitant reductions in strength or performance, will be considered indicative of successful DOMS induction. Creatine kinase (CK), an indicator of muscle damage, will also be assessed to ensure that DOMS has been successfully induced (4).

#### Days 1–5: intervention and recovery

2.5.3

Following DOMS induction, participants will be assigned to one of three interventions: IH, HH, or control (placebo). Sessions will take place in a controlled environment using a normobaric hypoxia generator. Each session will last 42 min, with participants seated in a reclined position, using the MITOVIT Hypoxic Training System (MITOVIT, Germany). The device automatically adjusts the intensity of the hypoxic or hypoxic–hyperoxic stimulus (FiO_2_) according to individual physiological data collected during the trial session.

##### IH group

2.5.3.1

Participants will remain at rest and undergo intermittent hypoxia with a 5:2 ratio. Each cycle will consist of 5 min of hypoxia (FiO_2_ ≈ 12%; which corresponds to a simulated altitude of ∼4,300–4,500 m) followed by 2 min of normoxia (FiO_2_ ≈ 21%), totaling six cycles per session. This protocol yields 30 min of hypoxia per session, aiming to achieve an 85% oxygen desaturation threshold. This range safely and effectively activates HIF-1α, triggering cellular adaptations related to angiogenesis, energy metabolism, and mitochondrial biogenesis (22, 23). Each session will last 42 min. IH has been proposed as a non-pharmacological strategy to enhance recovery and physiological adaptations (24).

##### HH group

2.5.3.2

Participants will remain at rest and undergo hypoxia–hyperoxia with a 5:2 ratio. Each cycle will include 5 min of hypoxia (FiO_2_ ≈ 12%) followed by 2 min of hyperoxia (FiO_2_ ≈ 30%–35%), averaging six cycles per session and totaling 42 min. The protocol aims for a mean desaturation of 85% (25, 26).

The choice of 5-minute hypoxic blocks as the standard duration is based on scientific evidence indicating that this interval is optimal for effectively activating HIF-1α without compromising cellular safety (27).

##### Control group

2.5.3.3

Participants will remain at rest and will be exposed to continuous normoxia (FiO_2_ ≈ 21%) for 42 min, serving as a reference condition. All participants will remain seated in a relaxed position, breathing through a mask connected to the hypoxia generator. This placebo condition ensures that observed effects are attributable to the active interventions.

#### Safety considerations

2.5.4

Peripheral oxygen saturation (SpO_2_) and heart rate will be continuously monitored. The system is equipped with two pulse oximeters and prevents SpO_2_ from dropping below the safety threshold of 80%. In addition to real-time SpO_2_ and heart rate monitoring, participants will be verbally screened before each session for symptoms such as dizziness, nausea, headache, excessive fatigue, or discomfort related to mask use (24).

Adverse events will be defined as any unfavorable or unintended signs, symptoms, or physiological responses occurring during or after the intervention sessions, whether or not they are considered related to hypoxic exposure (19). Criteria for immediate interruption of the session will include a sustained SpO_2_ below 80%, abnormal cardiovascular responses, onset of moderate-to-severe symptoms, or participant request to stop the session (24).

In the event of an adverse response, the hypoxic stimulus will be immediately terminated, normoxic breathing will be restored, and the participant will be placed in a seated or supine position as appropriate (24). All adverse events will be documented and reported, and participants experiencing significant adverse responses will be withdrawn from the study and referred for medical evaluation if necessary (19).

Participants will also be advised to drink water after each hypoxia session. Equipment will be disinfected after use with an ozone treatment box (Ozone Treatment and Disinfection Box, JBM, Spain) to eliminate bacteria, viruses, and fungi.

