### Interventions and protocol

2.5

The intervention process will last for five days (Figure 1), with breathing intervention administered from Day 1 following the DOMS induction protocol. All participants will be instructed to maintain their habitual training routines.

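### The adverse event window opens only at the first breathing session, so it misses the first hypoxic exposure and events confined to the pre-session procedures, and from then on it counts the soreness the trial induces on purpose

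*Protocol article*

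**What the plan says.** **Definition.** Section 2.5.4 (Safety considerations) states: "Adverse events will be defined as any unfavorable or unintended signs, symptoms, or physiological responses occurring during or after the intervention sessions". The full clause also settles causality, because it includes events "occurring during or after the intervention sessions, whether or not they are considered related to hypoxic exposure". All such events are to be documented and reported, and a participant with a significant adverse response is withdrawn.

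**When sessions start.** Section 2.5 describes a five-day process "with breathing intervention administered from Day 1 following the DOMS induction protocol". Section 2.5.3 likewise places the assigned interventions after induction.

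**What comes earlier.** Section 2.5.1 says: "During the week prior to DOMS induction and intervention, all participants will attend a familiarization session". At that visit participants "undergo an initial graded exercise test to determine VO_2_max, and complete an initial hypoxia trial session". Section 2.5.2 then puts baseline measurements and the four-exercise hamstring protocol on Day 1.

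**What the induction is meant to produce.** Section 2.5.2 says: "A clinically significant increase in perceived muscle soreness, along with concomitant reductions in strength or performance, will be considered indicative of successful DOMS induction". It cites earlier work showing these effects 24 to 72 hours after exercise, and it adds CK as a further check.

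**The concern.** The definition appears to be drawn in the wrong place at both ends.

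It opens too late. The procedures before the first breathing session include a first exposure to hypoxia in people with no previous hypoxia training (an exclusion criterion in section 2.2), a maximal treadmill test, and heavy eccentric loading. The Day 0 trial also comes before the stimulus has been individualised, because the device uses data from that trial to set later sessions.

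Once open, it is too broad. It makes no exception for the muscle response that the design sets out to create in every participant. A count of participants with any event would then mostly describe successful induction and say little about how the gas mixtures were tolerated.

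The abstract hopes the findings may inform policy on safe use of hypoxia in sports medicine. An event report with these boundaries would be weak support for that. There is also a knock-on effect: if intended soreness is an adverse event, a strong but intended response could be read as triggering the withdrawal rule, with loss of data on hamstring strength, the primary endpoint.

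**Working it through.** The protocol gives no adverse event rate, safety endpoint or safety test, so there is no figure to reproduce. The check is on timing and wording, with some counting.

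**1. Order of procedures against the window**

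| Procedure | Timing | Event confined to it is inside the definition? |
|---|---|---|
| Graded exercise test | Day 0 (2.5.1) | No |
| Hypoxia trial session | Day 0 (2.5.1) | No |
| Baseline tests | Day 1, before induction (2.5.2) | No |
| DOMS induction | Day 1, before session 1 (2.5, 2.5.2) | No, unless it persists or emerges after session 1 |
| Breathing sessions | Days 1 to 5 (2.5.3) | Yes |

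The Day 0 trial cannot be read as an intervention session, because section 2.5.1 dates it to the week before both induction and intervention.

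**2. Size of the omitted part**

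Inputs: 45 participants, 15 per arm (2.4); two active arms; one session a day on Days 1 to 5; placebo sessions in continuous normoxia (2.5.3.3). Assume everyone completes the schedule.

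- Day 0 hypoxic exposures: 45.
- Session exposures: 30 × 5 = 150.
- Total: 45 + 150 = 195. Share outside the window: 45 / 195 = 23%.
- Placebo arm: 15 exposures, all on Day 0, so all outside.
- Induction load per participant: 5×5 + 5×8 + 5×8 + 5×8 = 145 repetitions, of which 40 are at 130% 1RM.

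**3. Intended soreness inside the definition**

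Soreness and strength loss are expected 24 to 72 hours after induction, hence after session 1. They are unfavourable responses, and relatedness to hypoxia is not required. Read literally, they count.

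To show the effect on an any-event tally, let *p* be the risk of an event other than soreness and *s* the proportion with soreness, independent of *p* and equal across arms. Then P(any event) = 1 − (1 − *p*)(1 − *s*), and the difference between arms shrinks by the factor (1 − *s*). The values of *p* below (10% on placebo, 40% on active) are assumed and do not come from the protocol.

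| *s* | Placebo | Active | Difference |
|---|---|---|---|
| 0 | 10% | 40% | 30 points |
| 0.5 | 1 − 0.9×0.5 = 55% | 1 − 0.6×0.5 = 70% | 15 points |
| 0.9 | 1 − 0.9×0.1 = 91% | 1 − 0.6×0.1 = 94% | 3 points |
| 1.0 | 100% | 100% | 0 |

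**4. Do the omitted events distort the arms?**

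Put *c*, a common risk of an event before session 1, in place of *s*. With *c* = 10% the arms become 19% and 46% (27 points). With *c* = 30% they become 37% and 58% (21 points). Leaving such events out therefore does not create or hide an arm difference; it under-reports what trial participation involves. It also follows that widening the window into one pooled count would dilute the contrast further, so the fix must record which procedure each event followed.

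**The case against.** The strongest reply is that there is no safety comparison to spoil. Section 2.5.4 promises only documentation and reporting, section 2.6 has no safety endpoint, and section 2.7 has no event analysis. Events can be listed by type, and section 2.5.4 already names symptoms to screen for before each session. This stands. A reader might infer that the comparison between arms is wrong, or that every arm will report 15 of 15 participants with an event. The documents support neither: they commit to no single any-event incidence, and Day 0 and induction are common to all arms and precede the allocated treatment.

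Second, a reader might infer that every injury from the induction goes unreported. That is too strong. Session 1 follows induction on the same day and causality is irrelevant, so harm still present or appearing after session 1 is captured. What is lost is harm that resolves before session 1, or that occurs in someone who never reaches it.

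Third, soreness, strength and CK are already collected as outcomes, and rules on expectedness may be left to a fuller protocol. The first half is true and makes the remedy easy. The second half does not dispose of the point: the article states a definition with a fixed opening and an explicit causality rule, and its wording takes in the intended response.

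**Conclusion.** The point holds as a badly set boundary in a stated rule. Followed as written, it leaves out events confined to the Day 0 hypoxia trial (45 of 195 planned hypoxic exposures, 23%, and all of the placebo arm's), the Day 0 exercise test, the Day 1 baseline tests and the induction. From session 1 it mixes intended muscle soreness with possible harms of the breathing intervention. The consequence is incomplete and diluted safety reporting. It is not bias between arms, and it changes neither the primary analysis nor the sample size.

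The 23% assumes full attendance by 45 participants. The dilution figures rest on assumed event rates and on soreness being independent of other events and equal across arms; they matter only if an any-event count is tabulated. If an intervention did alter soreness, the event count would partly duplicate an efficacy outcome.

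The point is modest, but worth correcting before data are collected under this definition.

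**What to change.** 1. In section 2.5.4, start the adverse event window at the first Day 0 procedure, so that it covers the hypoxia trial, the exercise tests, the induction and the breathing sessions.
2. Add a field to the event form for the procedure each event followed, so that events before session 1 can be shown apart from those after it.
3. State that expected DOMS (soreness, strength loss, CK rise) is reported as an outcome. Tabulate it separately from the hypoxia-type symptoms already screened (dizziness, nausea, headache, mask discomfort), by arm. Excessive fatigue, also on the screening list, could come from either source, so say where it will be tabulated.
4. The investigators should reconcile three passages: the adverse event definition, the intended response in section 2.5.2, and the rule in section 2.5.4 withdrawing participants after a significant adverse response. How they are reconciled is a clinical matter, and no threshold or referral rule is suggested here.

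Cost: a few sentences and one form field. The downside is slightly more events to record from Day 0 and Day 1.

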### Sample size

2.4

The primary outcome of this trial is hamstring isometric strength. The required sample size was determined *a priori* using G*Power 3.1 considering a repeated measures of variance (ANOVA) design. In the absence of prior data to inform the expected magnitude of change, a conventional medium effect size (*f* = 0.25), as defined by Cohen, was assumed. With a significance level of *α* = 0.05, a statistical power of 0.80 (*β* = 0.20), and six time points, the analysis indicated that 36 participants would be required to detect statistically significant differences between groups. To account for potential dropouts and non-compliance, an additional 20% contingency was applied, increasing the total sample size to 45 participants (15 per group).

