### Outcomes

2.6

Table 1 summarizes the assessment moments of the different outcomes. All outcome assessments will be conducted following a standardized temporal sequence throughout the study period (19). Baseline measurements (Day 0) will be performed prior to DOMS induction and before any hypoxic exposure (19).

**Table 1 T1:** Assessment moments of the different outcomes.

Outcome	Assessment moments
Descriptive variables	Day 0
Physical Recovery variables	Days 1, 2, 3, 4, 5
VO_2_max	Days 0 and 5
Hamstring isometric strength	Days 1, 2, 3, 4, 5
Cognitive function (D2, TMT A/B) and stress (DASS-21)	Days 0 and 5
Psychological profile (CPRD)	Day 0
Sprint 30 m	Days 1, 2, 3, 4, 5
Counter Mouvement Jump (CMJ)	Days 1, 2, 3, 4, 5
Squat 1-RM	Days 1, 2, 3, 4, 5
Inflammatory and recovery biomarquers (HIF-1α, PGC-1α, Lactate, Klotho, CK)	Days 1, 2, 3, 4, 5

On Days 1 to 5, all daily assessments of physical recovery, neuromuscular performance, autonomic nervous system activity, and biochemical markers will be performed at the same time of day for each participant (19). Physical performance outcomes will be collected following a standardized warm-up (28).

The study outcomes will be hierarchically structured as follows: hamstring isometric strength will serve as the primary endpoint; additional physical performance, recovery, and biochemical variables will be treated as secondary endpoints; and cognitive and psychological measures will be analyzed on an exploratory basis.

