### Statistical analysis

2.7

All statistical analyses will be performed using IBM SPSS Statistics version 29 (IBM Corp., Armonk, NY, USA). The primary confirmatory analysis will focus on hamstring isometric strength. The normality of the variables will be assessed using the Shapiro–Wilk test. Descriptive analysis will be performed using the mean ± standard deviation for normally distributed data, or the median and interquartile range for data not following a normal distribution.

The principal analysis will evaluate the Group × Time interaction using repeated-measures ANOVA, as this term reflects the differential effect of the intervention over time between groups. When significant interaction or main effects are observed, Bonferroni-adjusted *post hoc* comparisons will be conducted. Effect size will be evaluated using partial eta squared (*η*^2^*p*).

Analyses will be conducted according to the intention-to-treat principle, including all randomized participants in the groups to which they were allocated. Missing data will be handled using multiple imputation procedures under the missing-at-random assumption prior to conducting the repeated-measures ANOVA.

Secondary outcomes will be analyzed using the same analytical approach. Where multiple comparisons across secondary endpoints are conducted, Bonferroni correction will be applied within each family of related outcomes.

Cognitive and psychological variables will be analyzed on an exploratory basis. Correlation analyses (Pearson or Spearman) and multiple linear regression models will be performed to explore potential associations and predictors of cognitive improvement or functional recovery. The level of statistical significance will be set at *p* < 0.05.

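### Section 2.5.4 removes participants with significant adverse responses from the study, not only from the breathing sessions, so the all-randomized analysis has to impute outcomes that could have been measured

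*Protocol article*

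**What the plan says.** Section 2.5.4 (Safety considerations) describes two separate steps. The first acts on the session: "Criteria for immediate interruption of the session will include a sustained SpO_2_ below 80%, abnormal cardiovascular responses, onset of moderate-to-severe symptoms", with a participant's own request as a further ground. The second acts on participation as a whole: "participants experiencing significant adverse responses will be withdrawn from the study and referred for medical evaluation if necessary". The article does not define which responses count as significant, and it does not say that outcome assessment continues after such a withdrawal.

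Section 2.4 names the endpoint: "The primary outcome of this trial is hamstring isometric strength". Table 1 in Section 2.6 schedules it daily: "Hamstring isometric strength Days 1, 2, 3, 4, 5".

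Section 2.7 sets the analysis population: "Analyses will be conducted according to the intention-to-treat principle, including all randomized participants in the groups to which they were allocated". It then deals with gaps: "Missing data will be handled using multiple imputation procedures under the missing-at-random assumption prior to conducting the repeated-measures ANOVA".

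Exposure differs by arm. Sections 2.5.3.1 and 2.5.3.2 give IH and HH blocks at an inspired oxygen fraction of about 12%, aiming at 85% saturation. Section 2.5.3.3 gives the control arm about 21% throughout.

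**The concern.** An intention-to-treat analysis is strongest when outcomes are observed whether or not treatment was completed. Here the protocol itself ends observation for people who react badly to what they breathe. Those people are likely to be more numerous in two of the three arms. The analysis then fills their later strength values using "multiple imputation procedures under the missing-at-random assumption". That treats withdrawal as uninformative about the unseen outcome once the observed data are taken into account.

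If people who tolerate the sessions poorly also recover more slowly, the imputed values are too good and the active arms look better than they are. If they recover no differently, little harm is done. The trial could not tell these cases apart, because the values that would decide the matter are never collected. With 15 participants per arm, one or two such people are enough to matter for interpretation. No later analysis plan can restore measurements that were not taken.

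**Working it through.** **1. The plan's own figure.** Section 2.4 gives 36 participants before dropout and a 20% contingency. 36 / (1 − 0.20) = 45, and 45 / 3 = 15 per group. The stated total reproduces. Twenty per cent of 15 is 3, used below as an upper case. The plan's 20% covers all dropout and non-compliance in every arm, so 3 adverse-event withdrawals in one arm is a high figure.

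**2. Yardstick for size.** Section 2.4 assumes f = 0.25. For three equally spaced group means (an assumption, ignoring the repeated measures), the largest pairwise difference is f × √6 = 0.25 × 2.449 = 0.61 SD.

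**3. Formula.** Let k be the number withdrawn in an active arm of 15, and d the amount, in SD, by which their unobserved strength falls short of what imputation assigns them. The arm mean shifts by (k / 15) × d. This takes the arm to be in the imputation model (Section 2.7 does not give the model) and no post-induction strength value to be available before withdrawal.

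**4. Inputs not in the documents.** Both k and d are assumptions. k runs from 1 to 3. d runs from 0.25 to 0.6 SD. The upper end corresponds to losing the whole of the 0.61 SD design difference. A deficit of 1 SD is shown only as an extreme, since it exceeds that difference.

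| Withdrawn | d = 0.25 | d = 0.6 | d = 1 (extreme) |
|---|---|---|---|
| 1/15 | 0.02 | 0.04 | 0.07 |
| 2/15 | 0.03 | 0.08 | 0.13 |
| 3/15 | 0.05 | 0.12 | 0.20 |

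As a share of 0.61 SD, the main range runs from about 3% (0.017 / 0.61) to 20% (0.12 / 0.61). The extreme is 33% (0.20 / 0.61).

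**5. Check by simulation.** The simulation had 15 per arm, no treatment effect, a baseline-to-outcome correlation of 0.5, and regression imputation on baseline and group. With a withdrawal probability of 0.20 in the active arm and d = 1, the difference using everyone's actual outcome averaged −0.20 SD, and after imputation 0.00. With probability 1/15 and d = 0.25 the two were −0.02 and −0.01. Both agree with the formula within simulation error.

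**6. When the shift is smaller.** Only values after withdrawal are imputed. A participant withdrawn on Day 3 or 4 has earlier post-induction values, and if these already show slower recovery the imputation can use them. A participant withdrawn at the first session has little beyond the Day 1 measurement. With continued assessment the values are observed, and the shift from this source is zero.

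**The case against.** Several points on the other side are sound.

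- **A reader might take the desaturation, cardiovascular and symptom criteria to be the triggers for withdrawal, and so expect many losses.** The text does not support that. Those criteria interrupt a session. Withdrawal needs a significant adverse response, which is a separate and undefined step.
- **A reader might infer that losses occur in the active arms only.** Section 2.5.4 counts events whether or not they relate to hypoxia, and its symptom screen includes mask discomfort, which any arm can have. The documents support more often, not only.
- **Screening may keep the number low.** Section 2.5.1 gives every participant a hypoxia trial session on Day 0. The abstract and Section 2.5.3 place allocation after the induction of soreness, so marked intolerance may appear before it can differ by arm. The device also adjusts the stimulus to each participant, and Section 2.2 excludes relevant disorders.
- **A reader might see a contradiction with intention-to-treat.** There is none. Section 2.7 promises to include everyone randomized in the allocated group, and imputing the missing values meets that wording.
- **Direction is not established.** Nothing in the documents links poor tolerance of hypoxia to slower hamstring recovery, and without the imputation model one cannot say that values come only from arm-mates.
- **Some assessments are strenuous.** The sprint, the squat test and the Day 5 maximal treadmill test may be unsuitable after an adverse response, so not all missingness is avoidable.

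These points limit the number of withdrawals, the size and the certainty of direction. They leave standing that the article ends participation at study level, states no continued assessment, and relies on missing-at-random for the values then lost. Both rules are written in the article, so this is not a detail left to a fuller document.

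**Conclusion.** The point holds as an avoidable weakness in the primary analysis, not as an error or an internal contradiction. A stated rule creates missing primary-outcome data tied to the response to the intervention, probably more often in IH and HH, and the all-randomized estimate then depends on an untestable assumption about those people.

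The plausible size is modest: about 0.02 to 0.12 SD in an active arm's mean, and 0.20 SD only at the extreme. This rests on assumed withdrawals of 1 to 3 of 15, an assumed deficit of 0.25 to 0.6 SD, and no post-induction strength value before withdrawal. A bias in favour of the active arms requires that those withdrawn would have recovered worse. A reader might take that as given, but the documents do not show it. The required sample size is unaffected.

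**What to change.** Leave the session-interruption and treatment-stopping criteria exactly as they are; they are clinical matters and are not judged here. In Section 2.5.4, distinguish ending the breathing sessions from ending follow-up. State that hamstring strength, and the other scheduled assessments where appropriate, continue to Day 5 unless the participant withdraws consent or the medical evaluation advises against testing. In Section 2.7, add that data collected after sessions end are analysed in the allocated arm.

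The cost is two sentences and, at most, a few visits that are already scheduled, for participants who have stopped sessions. The change has to be made before data collection, since missed outcomes cannot be recovered. A sensitivity analysis that departs from missing-at-random would be a useful addition for any remaining gaps, but it is optional and may sit in the SAP.
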